##### Primary analysis

The primary endpoint, the number of migraine days in the last 4 weeks of treatment, will be measured twice for each patient, once after the placebo treatment period and once after the IMP treatment period. The number of migraine days in the 4 weeks before start of treatment will be assessed for both treatment periods, thus there will be two baseline values that will be used as covariates. This process has the aim of correcting for any potential seasonal variation in baseline migraine frequency or carry-over effects.

The primary analysis will be performed using a linear, mixed-effects regression model. The primary model will include the primary endpoint (the number of migraine days in the last 4 weeks of treatment) as the response variable, the respective baseline value as a covariate, treatment (IMP vs placebo) and period (first vs second) as main effects, the two interaction terms “treatment × period” and “treatment × baseline value”, and patient as random effects. A significant interaction term between treatment and period would indicate a carry-over effect. Since it is not known how strongly the primary endpoint correlates with the baseline value, it is not known whether including the baselines as covariates in the model is sensible. Therefore, the already described primary model will be compared to models without the interaction term “treatment × baseline value” and without both the interaction term “treatment × baseline value” and the baseline value as a covariate by means of Akaike’s Information Criterion (AIC).

The primary analysis will be done on the ITT set.

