#### Fixed sample size estimation

##### Assumptions

Sample size estimation is based on the following assumptions:We expect the baseline number of migraine days per 4 weeks to be 10 days in our patient population.Placebo effect: based on recent findings [64], we assume a rather strong placebo effect of 32% reduction in the primary endpoint. This corresponds to an absolute reduction of 3 migraine days per 4 weeks.IMP effect: synthesising previous findings [4, 64] and our pilot data [65], we aim to detect a difference of 2 days between placebo and IMP.We assumed the absolute reduction in migraine days to be normally distributed with a standard deviation of 3 days.We assume a conservative intra-patient correlation between IMP and placebo of 0.4.Drop out: a high drop-out rate of 30% is assumed.

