##### Re-sampling

The sample size was estimated using a re-sampling method. Each sample size (n_i_ = 1,...,49 = 12, ..., 60) was evaluated by sampling *R* = 999 times the reduction in migraine days from a bivariate normal distribution as already described. For each sample, whether superiority of the IMP over placebo could be shown (i.e. whether a two-sided paired *t* test resulted in significant *p* < 0.05) was tested.

In order to show the superiority of the IMP over placebo with a statistical power of 90%, 45 patients should be recruited in total to ensure 31 evaluable patients, assuming a drop-out rate of 30%. Figure 3 shows how the sample size depends on the expected reduction in number of migraine days in the IMP arm.

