### Statistical analyses

Detailed methodology for summaries and statistical analyses of the data collected in this study will be documented in a statistical analysis plan. The statistical analysis plan will be finalised before database closure and will be under version control at the CTU, University Hospital Basel.

The primary endpoint, the number of migraine days in the last 4 weeks of treatment, will be measured twice for each patient, once after the placebo treatment period and once after the IMP treatment period. The number of migraine days in the 4 weeks before the start of treatment will be assessed for both treatment periods, thus there will be two baseline values that will be used as covariates. This process has the aim of correcting for any potential seasonal variation in baseline migraine frequency or carry-over effects.

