##### Secondary analysis

The secondary (exploratory) objectives are to assess the therapeutic efficacy of externally induced mild ketosis by the IMP regarding the following secondary endpoints:change in number of headache days of any severity from baseline (meeting ICHD-3 criteria) during the last 4 weeks of intervention;change in number of headache days of any severity from baseline (meeting ICHD-3 criteria) during the last 4 weeks of follow-up;change in consumption of acute migraine medication from baseline (analgesics or triptans)— measured in days with acute headache medication use—during the last 4 weeks of intervention;change in average migraine intensity from baseline—assessed with a VAS from 0 to 10 for each migraine episode—during the last of 4 weeks of the intervention period; andchange in disability from baseline—assessed with the Migraine Disability Assessment (MIDAS) and the Headache Impact Test (HIT-6)—to the last of 4 weeks of the intervention period.

All of these secondary endpoints will be analysed as described for the primary endpoint with the corresponding baseline measure as covariate, if available.

All secondary analyses are done on the ITT set.

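### The primary model's baseline covariate mixes between-patient and within-patient slopes, which can cost precision in the treatment comparison but does not bias it or invalidate the sample size

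*Protocol article*

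**What the plan says.** The protocol article measures migraine days before each treatment period: "thus there will be two baseline values that will be used as covariates" (Statistical analyses, repeated under Primary analysis). The stated purpose is to correct for seasonal change or carry-over.

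The Primary analysis section defines a linear mixed model for migraine days at the end of each period. It contains "the respective baseline value as a covariate", treatment, period, treatment × period, treatment × baseline, and patient as random effect. The protocol says that the strength of the link between baseline and endpoint is unknown. It therefore uses AIC to compare this model with one without treatment × baseline and one without any baseline term.

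The Secondary analysis section extends the same form: "All of these secondary endpoints will be analysed as described for the primary endpoint".

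The sample size does not rest on this model. It rests on simulated reductions in migraine days, each data set being tested by whether a "two-sided paired *t* test resulted in significant *p* < 0.05".

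**The concern.** In a two-period crossover the treatment effect is estimated from each patient's difference between periods. A baseline covariate helps only as far as a change in a patient's own baseline predicts a change in that patient's own outcome. That is the within-patient slope. The between-patient slope describes something else: patients with a high usual frequency stay high. It can be large even when the within-patient slope is near zero.

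A single baseline term in a random-patient model estimates a blend of the two. If the blend lies well above the within-patient slope, the model over-adjusts. Random differences between a patient's two baselines then enter the treatment contrast as noise.

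The safeguards in the plan do not address this. Treatment × baseline lets the slope differ by treatment, but each of those slopes is still a blend. AIC scores the whole fit, including how well baseline explains differences between patients, and no candidate model has separate slopes. At stake is precision in a trial that reports slow recruitment and allows for 30% drop-out.

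**Working it through.** **1. The plan's own figure.** Inputs from the Assumptions list: "we aim to detect a difference of 2 days between placebo and IMP"; "We assumed the absolute reduction in migraine days to be normally distributed with a standard deviation of 3 days"; "We assume a conservative intra-patient correlation between IMP and placebo of 0.4".

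- SD of the paired difference = √(2 × 3² × (1 − 0.4)) = √10.8 = 3.286.
- Standard error at n = 31: 3.286/√31 = 0.590.
- Noncentral-t power, two-sided 5%: 0.896 at n = 30 and 0.906 at n = 31.
- Drop-out: 31/0.7 = 44.3, rounded up to 45.

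This reproduces "with a statistical power of 90%, 45 patients should be recruited in total to ensure 31 evaluable patients".

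**2. The mechanism.** Let dY and dB be a patient's IMP-minus-placebo differences in endpoint and baseline. Adjusting with slope b gives the contrast dY − b·dB, with

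Var = Var(dY) − 2b·Cov(dY, dB) + b²·Var(dB).

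This is smallest at the within-patient slope βw = Cov(dY, dB)/Var(dB). Any other b adds (b − βw)² × Var(dB).

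**3. A worked case that keeps the protocol's inputs.** The protocol gives no baseline SD and no baseline correlations, so these are assumptions: equal SDs for baseline and endpoint; correlation 0.7 between baseline and endpoint in the same period, 0.68 across periods, and 0.8 between the two baselines and between the two endpoints.

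- SD of change 3 requires 2s²(1 − 0.7) = 9, so s² = 15.
- Covariance of the two changes = 15 × (0.8 − 2 × 0.68 + 0.8) = 3.6, and 3.6/9 = 0.4, as the protocol assumes.
- Within-patient slope = (0.7 − 0.68)/(1 − 0.8) = 0.10. Between-patient slope = (0.7 + 0.68)/(1 + 0.8) = 0.77.
- Var(dB) = Var(dY) = 2 × 15 × 0.2 = 6.
- The slope fitted by the single-covariate model in simulation was 0.58.

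Standard error with 31 pairs = √[6 × (1 − 2b × 0.10 + b²)/31]:

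| Slope used | Standard error |
|---|---|
| b = 0.10 (within-patient) | 0.438 |
| b = 0.58 (blended) | 0.486 |
| b = 1 (change score) | 0.590 |

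Simulation with estimated slopes gave 0.443 (separate slopes) and 0.488 (single slope), with power 99.2% and 97.6%. The variance ratio is (0.488/0.443)² = 1.21.

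The last row equals the standard error in step 1. The sample size is that of a change-score analysis, which fixes the slope at 1. In this case the blended slope costs precision against the best model and still does better than the planning calculation.

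**4. Range on the protocol's inputs.** Simulations with 31 complete pairs, SD of change 3, correlation of changes 0.4 and difference 2 days; the between-patient SD is assumed:

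| Setting | SD of estimate, single | SD of estimate, separate | Variance ratio |
|---|---|---|---|
| Within-patient slope near zero, between-patient SD 2 | 0.489 | 0.455 | 1.16 |
| Within-patient slope near zero, between-patient SD 3 | 0.486 | 0.413 | 1.38 |
| Slopes similar | 0.496 | 0.500 | 0.98 |

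The last row shows no difference beyond simulation error.

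Gains in power from separate slopes were −0.3 to +1.6 points in one set of settings. They were 0.3 to 1.5 points in a set with the run-in baseline limited to 5–14 days, and 0.5 to 3.6 points in a set with between-patient SD 2 to 4 (simulation error there up to about 1 point). Overall this is about 0 to 3 points. Single-slope power stayed at about 95% or more.

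**5. The safeguards.** AIC kept a baseline term in 76 to 100% of runs. Power with treatment × baseline was within about 1 point of the single-slope model. Type I error of the single-slope model was 0.048 to 0.054.

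**The case against.** The strongest reply has four parts.

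- **It is a legitimate choice.** A period-specific baseline in a mixed model is common, and the error rate is sound. This stands: the point concerns efficiency only.
- **The within-patient slope may not be near zero.** The second baseline is collected because of seasonal variation, which would shift a patient's baseline and outcome together. This also stands. With slopes of 0.40 and 0.53 the single-slope model had 97.3% power against 97.0% with separate slopes, and 94.8% with no covariate. The protocol itself calls the relevant correlation unknown, however, so a model that relies on equal slopes is a weak default.
- **Eligibility limits patient spread.** The 5–14 day range applies to the four months before screening and again to the run-in. This narrows differences in usual level and makes the larger losses less likely. It does not remove the mechanism.
- **Detail belongs in the SAP.** The protocol defers detail, but it does fix the form of the covariate and the list of AIC candidates, and none separates the slopes.

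A reader might also infer that power falls below 90%, with losses up to 8 or 9 points. Such figures arise if the two changes are simulated as uncorrelated (for example 86.3% against 93.3% at between-patient SD 4), or if SD 3 and correlation 0.4 are applied to the raw endpoint (up to 9.2 points with zero within-patient slope). The protocol supports neither: it attaches the SD to the reduction and draws the two reductions from a bivariate distribution with correlation 0.4.

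A reader might further infer bias, since the Background suggests that protection could persist after ketosis ends. A residual effect on the second baseline could pass into the estimate through the blended slope. The protocol gives no size or duration for such an effect, so this remains conjecture.

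**Conclusion.** The point holds as a conditional loss of efficiency. The baseline slope in the primary model mixes two relations although treatment is compared within patients, and neither the interaction nor AIC corrects this. On the protocol's planning inputs the cost is about 0 to 3 points of power at a difference of 2 days, with power above 90%. Power is close to its ceiling there, so the variance is the better measure. It is about 10 to 40% larger than needed when the within-patient slope is near zero and patients differ clearly in usual level, and not materially larger when the slopes are similar.

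The sizes rest on assumed baseline variances and correlations, normal data and complete pairs. The stated 31 and 45 patients are right, and the ordinary type I error is unaffected. Neither a general loss of several points nor power below 90% follows from the document.

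**What to change.** In the Primary analysis section, and in the SAP before database closure, replace the single baseline covariate by two:

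- the patient's mean of the two baselines;
- the deviation of the respective baseline from that mean.

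Keep treatment, period and the random patient effect. Patients with only one baseline take that value as the mean and 0 as the deviation. Use the same form for secondary endpoints with period-specific baselines. Reword treatment × baseline and the AIC candidates to match.

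The cost is one or two sentences and one degree of freedom, with no new data. If the slopes are in fact equal, the loss is a fraction of a point of power.

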#### Hypothesis

The *null hypothesis* is that there is no difference in the difference in number of migraine days per 4 weeks from baseline to the last 4 weeks of intervention between the IMP and the placebo treatment.

The corresponding *alternative hypothesis* is that the difference in the number of migraine days per 4 weeks from baseline to the last 4 weeks of intervention differs between the IMP and the placebo treatment.

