#### Handling of missing data and drop-outs

The frequency of, timing of and reasons for, as well as all side-effects of, drop-outs will be reported for each treatment. Patients who drop out during the first run-in period or during the first 4 weeks of the first treatment period will be excluded. All patients who drop out later will be included in the ITT set.

For patients who drop out after the first 4 weeks and before the end of the first treatment period, the primary endpoint for the first treatment period will be imputed using multiple imputations. If appropriate, imputations will be accounted for baseline value and number of migraine days during the first treatment period, as far as available. The primary endpoint for the second treatment period will not be imputed for these patients.

For patients who drop out after the end of the first treatment period and before the first 4 weeks of the second treatment period are finished, the primary endpoint for the second treatment period will not be imputed. The primary endpoint for the first treatment period will be available.

For patients who drop out after the first 4 weeks and before the end of the second treatment period, the primary endpoint for the second treatment period will be imputed as already described.

Thus, for each patient included in the ITT set, the primary endpoint will be available (whether measured or imputed) for at least the first treatment period and will be taken into account with the proposed mixed effects models.

In case there are indications for missing data not at random, the inverse probability of censoring weights (IPCW) will be considered.

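### The model behind the primary test is left to an AIC comparison on the trial's own outcome data, with no fixed treatment contrast and with the baseline allowed to drop out

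*Protocol article*

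**What the plan says.** Under Primary outcome measure, the outcome is the change from baseline in migraine days. Under Hypothesis, the null is "no difference in the difference in number of migraine days per 4 weeks from baseline to the last 4 weeks of intervention" when IMP and placebo are compared. The opening of Statistical analyses, repeated under Primary analysis, commits to the two baseline counts as covariates, to correct for seasonal variation or carry-over.

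Primary analysis then sets out a linear mixed model for the raw count in the last 4 weeks. Its terms are the period's own baseline, treatment, period, treatment × period, treatment × baseline and a random patient effect. The section next says it is unknown whether adjusting for baseline is sensible, and goes on: "Therefore, the already described primary model will be compared to models without the interaction term" of treatment with baseline, and to one lacking both that term and the baseline. The criterion is AIC. All three candidates keep treatment × period, which the section treats as the indicator of carry-over.

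The section does not say which model supplies the p-value, which treatment contrast is tested, or how treatment, period and baseline are coded. Sensitivity analysis lists only a repeat on the per-protocol set. Under Handling of missing data and drop-outs, for patients who leave after the first 4 weeks but before the end of that period, "the primary endpoint for the first treatment period will be imputed using multiple imputations"; the second period is treated in the same way.

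**The concern.** A confirmatory test needs one model and one contrast, fixed before outcomes are seen. Here the comparison uses the outcome data, and every candidate contains treatment.

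The treatment coefficient also changes meaning between candidates. With 0/1 coding and uncentred baseline, it is the effect in period 1 at a baseline of zero migraine days in the full model. Zero lies outside the eligible range of 5 to 14. In the other two models it is the period 1 effect, adjusted for baseline or not.

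If the third candidate wins, baseline leaves the primary analysis altogether. This conflicts with the stated outcome, the hypothesis and the covariate commitment. The open choice spreads further, because the subgroup models, the secondary endpoints and several exploratory endpoints are all built on the primary model.

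**Working it through.** **1. The plan's own figure.** Inputs from Assumptions and Re-sampling: "we aim to detect a difference of 2 days between placebo and IMP"; "We assumed the absolute reduction in migraine days to be normally distributed with a standard deviation of 3 days"; "We assume a conservative intra-patient correlation between IMP and placebo of 0.4"; power counted as the share of samples in which a "two-sided paired *t* test resulted in significant *p* < 0.05"; 90% power; 30% drop-out.

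- SD of the paired difference = √(2 × 3² × (1 − 0.4)) = √10.8 = 3.286.
- Power from the noncentral t: 89.6% at n = 30 and 90.6% at n = 31, so 31 is the smallest adequate number.
- 31 / (1 − 0.30) = 44.3, rounded up to 45.

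The stated 31 and 45 are reproduced. They come from a paired comparison and do not depend on the AIC step.

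**2. Why the coefficient moves.** In the full model the effect at baseline b is τ + γb. At the expected mean baseline of 10 days it is τ + 10γ, so the uncentred coefficient is τ = (effect at mean baseline) − 10γ. For one extra parameter, AIC keeps γ when the likelihood-ratio statistic exceeds 2, that is, when |γ̂| is above about √2 = 1.41 standard errors. The full model is therefore chosen in just those data sets where γ̂ is large by chance, and there τ̂ is shifted by 10γ̂.

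**3. Simulation of the three candidates.** AIC came from maximum-likelihood fits, and the selected model was tested by a REML Wald t at 5%.

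- From the document: change SD 3, correlation of the two changes 0.4, mean baseline 10.
- Assumed, not in the document: baseline SD 2.5; correlation between the two baselines 0.5; endpoint-baseline correlation 0, 0.3, 0.5 or 0.7 within a period, and 0.8 times that across periods.
- Sizes: 31 complete patients, or 45 of whom 31 have a second period.
- 5,000 null trials per setting, so the Monte Carlo SE is √(0.05 × 0.95 / 5000) = 0.3 points.
- Power: 2,000 trials with a 2-day effect, n = 31, correlations 0.3 to 0.7.

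| Quantity | Contrast averaged over periods, at mean baseline | Coefficient as coded (0/1, uncentred) |
|---|---|---|
| Type I error, each model fixed in advance | 4.5-5.1% | 3.8-5.5% |
| Type I error, AIC-selected model | 4.8-5.4% | 7.3-8.9% |
| 95% CI coverage, AIC-selected (100% minus the row above) | 94.6-95.2% | 91.1-92.7% |
| SD of estimate, full model (days) | 0.36-0.59 | 1.65-2.87 |
| SD of estimate, baseline-only model (days) | 0.36-0.59 | 0.49-1.07 |
| Power, AIC-selected model | 92-99.5% | 42-56% |
| Power, baseline-only model fixed | 92-99.5% | 44-60% |

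A second simulation at n = 31, with the same baseline SD and range of endpoint-baseline correlations, gave 4.5-5.9% and 7.5-8.8% for the AIC-selected test.

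The low power in the last column comes from the contrast and not from the selection, because it appears with the baseline-only model fixed as well. With treatment × period in the model and 0/1 coding, the coefficient is a period 1 comparison between patients.

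**4. How often baseline drops out.** AIC chose the no-baseline model in 75-76% of null trials at an endpoint-baseline correlation of 0, 18-27% at 0.3, 1-4% at 0.5 and at most 0.1% at 0.7.

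**The case against.** The candidates and the criterion are named in advance, and AIC does not look at the treatment p-value. The section calls the full specification the primary model and never says outright that the lowest AIC supplies the result. Coding and contrast are normal SAP content, and the protocol promises an SAP before database closure. With a sensible contrast the error stays at about 5%.

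Much of this stands:

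- A reader might infer that AIC selection in itself invalidates the p-value and confidence interval. The averaged-contrast column shows otherwise; the inflation needs a reading that the protocol leaves open but does not state.
- A reader might count how often at least one of the three models is significant under the null (5.3-8.2% averaged, 8.9-11.4% as coded in these runs). That is the error of picking the smallest p-value, which is not the rule here.
- A reader might infer that dropping baseline biases the comparison. With randomised sequence and no carry-over into the second baseline, the raw-count and change contrasts have the same expectation. In these runs, the averaged contrast was also about equally precise with and without baseline.
- How AIC is combined over imputed data sets is SAP detail, though different imputations could favour different models.

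The SAP argument does not dispose of the point. The AIC comparison is a stated rule, introduced to settle whether baseline belongs in the model, and it is not labelled a sensitivity analysis. An SAP that keeps it still has to run it on outcome data. An SAP that replaces it departs from the protocol, which requires an amendment for substantial changes.

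**Conclusion.** The point holds as a failure to fix the primary model and its contrast. The protocol lets outcome data decide among three models and permits a result with no baseline in it, against its own outcome, hypothesis and covariate commitment.

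The numerical consequence depends on the contrast. Type I error is about 7-9% if the treatment coefficient is read as coded, with uncentred baseline, from the winning model. It is about 5% if the contrast is averaged over periods at mean baseline; the loss is then prespecification, adjustment and the match to the hypothesis. These ranges rest on the assumed baseline SD and correlations. The documents support neither a general claim that the test is invalid nor a claim of bias from omitting baseline. The sample size is unaffected.

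**What to change.** Name one primary model: migraine days in the last 4 weeks on treatment, period and the respective baseline, with a random patient effect and no data-driven selection. Name one contrast: IMP minus placebo averaged over the two periods, taken at mean baseline if any baseline interaction is kept.

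State whether treatment × period stays in that model, effect-coded so that it does not alter the contrast, or moves to a separate carry-over assessment. It should not disappear without comment, since all three candidates carry it. Report the treatment × baseline and no-baseline models as labelled sensitivity analyses whatever their AIC, and let the subgroup, secondary and exploratory analyses refer to the fixed model. The question of AIC across imputations then falls away.

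The cost is a few sentences in the protocol and SAP, with an amendment, and the option of choosing the model later. In the simulations, the baseline-only model with the averaged contrast had a type I error of 4.5-5.1% and power of 92-99.5% at 31 patients, so nothing is lost against the 90% target under those assumptions.
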